### Interventions

2.8

After the patients are enrolled, they will finish a questionnaire (baseline information) and the relevant examinations (48-h GITT, HRAM, FFD, BR, LKF). Previous studies have reported Forlax and Chinese herb as effective drugs for the treatment of TFC^[9]^ and aTFC^[20]^ respectively. So, the drug used for the treatment of TFC subtype is Forlax. The placebo will be a kind of white powder made from orange essence, saccharin sodium and dextrin (Shanghai Aipu Food Industry Corporation) according to 0.2:0.015:100 (w/w) and is similar to Forlax in shape and color. Both Forlax and placebo will be vacuum packaged as 10 g per pack using same type of aluminum foil. The drug in aTFC subtype will be Chinese herb powder dried by Chinese herb decoction (Tongrentang Chinese Medicine) from clinical prescription (see Table 2), and the placebo will be a kind of brown powder made from caramel pigment and dextrin (Shanghai Aipu Food Industry Corporation) at 0.4:10 (w/w). Both the Chinese herb powder and placebo will be vacuum packaged as 15 g per pack using same type of aluminum foil. The drugs and placebos will be taken twice a day, one pack at a time, flushed with warm boiled water, half an hour after breakfast and dinner. The contents of LVD are as following:

(1)Taboo spicy (especially chili, pepper), irritating food, wine, fried food, grilled food, dry nuts, mutton, leek, toonasinensis and so on.(2)Avoid meat, eggs, milk, drinking coffee and strong tea.(3)The staple food are cereals and grains, take vegetables and fruits as much as possible.(4)Eat medicinal gruel: millet (main ingredients), coix seed, red bean that are mixed and cooked and eaten 1 to 2 times a day.(5)More than half of the staple food is potato (such as sweet potato and potato).(6)Diet must accord with three meals a day, regular quantitative with abstinence from drinking

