**Table 2 T2:**
[figure not shown]
The component of Chinese herb powder.

Patients with diet intervention should follow the above items and patients without diet intervention will continue their previous eating habits. The treatment period will last for 28 days. During the treatment period, patients will be required to keep a diary about diet and defecation. The diet diary will be designed with a semi-quantitative food frequency method, and the defecation diary will gather information about sensation, stool shape and duration of each defecation. On the 14th day, patients will be followed up via telephone to find out the situation during the treatment and count the average times of CSBM per week, the average scores of constipation symptoms and TCM syndrome in the first 14 days. After 28 days of treatment, a second follow-up will be carried out to understand situation of constipation (the same to the first follow-up) and to ask the patients to finish the examinations (48-hour GITT, HRAM, BR, LKF). Fecal flora of fresh stool (<30 minutes) from patients will also be reviewed and the diaries will be taken back. During the intervention, the patients will keep in touch with the researchers for queries about the treatment if any to control the exit rate and any other drugs that can relieve constipation are forbidden.

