#### Safety outcomes

2.12.4

Safety parameters include AEs and laboratory examinations (BR, LKF).

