#### DQ and compliance measure

2.12.5

The number of qualified meals, total meals and the intake frequency of food involved will be calculated after getting the diary back. Diet high quality means a significant difference before and after intervention in diet groups, while there is no difference in non-diet groups. DCR means the ratio of qualified meals to total meals multiplied by 100. High compliance is achieved when DCR is more than or equal to 80%, while low DCR is less than 80%.

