### Planned statistical analysis

2.15

Continuous variables will be described as the mean ± standard deviation (SD), median or interquartile range (IQR). The number of cases, frequency, the rate and the constituent ratio will be described by categorical variables. Variance analysis will be used for continuous variables in the baseline data having normal distribution and same variance. Wilcoxon rank sum test or Kruskal–Wallis *H* test will be used for the comparison of differences between groups that are not normally distributed or have uneven variance. Categorical variables will be tested by chi–square test or Fisher exact test. Wilcoxon rank sum test or Kruskal–Wallis *H* test will be used for the number of CSBM per week in primary outcome. Chi–square test or Fisher exact test will be used for percent improvement of each symptom scale score in secondary outcome indicators. The result of 48-h GITT will be analyzed using chi-square or Fisher test. Wilcoxon rank sum test or Kruskal–Wallis *H* test will be used for measurement data in HRAM, while chi-square test or Fisher exact test will be used for counting data. Safety, dietary quality, compliance indicators will be tested by chi-square test or Fisher exact test. Wilcoxon rank sum test or Kruskal–Wallis *H* test will be used to compare the diversity, the relative abundance of bacteria in phylum and genera level between 2 or more groups.^[22]^ Complying with the intent-to-treat (ITT) and per-protocol (PP) principle, all data of the patients randomized and at least 1 assessment (include baseline assessment) will be analyzed. For dropouts and terminations, their missing data will be obtained by last-observation-carried-forward (LOCF) method. All statistical analyses will be performed by SPSS20 software (IBM, Chicago, Illinois), and *P* value <.05 will be considered statistically significant.

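### Section 2.15 names only a chi-square or Fisher test for safety, although safety includes measured blood, liver and kidney values; these should be analysed on their own scale

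*Protocol article*

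**What the plan says.** Section 2.15 (Planned statistical analysis) gives most outcomes their own test. For the outcomes at issue it says: "Safety, dietary quality, compliance indicators will be tested by chi-square test or Fisher exact test".

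Section 2.12.4 (Safety outcomes) defines what safety contains: "Safety parameters include AEs and laboratory examinations (BR, LKF"). The laboratory values are measured twice. Section 2.8 (Interventions) lists, at entry, "the relevant examinations (48-h GITT, HRAM, FFD, BR, LKF") and, after 28 days, plans "to ask the patients to finish the examinations (48-hour GITT, HRAM, BR, LKF").

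For compliance, section 2.12.5 gives a percentage, "DCR means the ratio of qualified meals to total meals multiplied by 100", and then a class: "High compliance is achieved when DCR is more than or equal to 80%, while low DCR is less than 80"%.

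Two other sentences of section 2.15 matter. A general sentence says that the Wilcoxon or Kruskal–Wallis test "will be used for the comparison of differences between groups that are not normally distributed or have uneven variance". The sentence immediately before the safety rule separates two kinds of manometry (HRAM) data: the Wilcoxon or Kruskal–Wallis "test will be used for measurement data in HRAM, while chi-square test or Fisher exact test will be used for counting data".

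**The concern.** Adverse events are counts, and a chi-square or Fisher test suits them. Haemoglobin, liver enzymes or creatinine are measurements. The only test named for the safety block cannot be run on them until somebody chooses a cut, and the article states none. Section 2.15 therefore sets a rule for these data rather than staying silent, and that rule discards information.

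The Discussion says that the trial will shed light on the safety as well as the effectiveness of a diet that avoids meat, eggs and milk. With 23 patients per arm, few values will lie outside a reference range. A test on normal versus abnormal then has little chance of showing that a laboratory value has moved, and its non-significance would say very little about safety.

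A lesser question is whether the compliance rate also loses information when it is compared only as high or low.

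**Working it through.** **Inputs from the article.** 23 patients per arm and 92 per subtype (section 2.6; 4 × 23 = 92, which reproduces). Significance at P < .05 (section 2.15), taken here as two-sided. The article gives no effect size, SD, power or laboratory cut, so everything below that needs one is an assumption.

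**Laboratory values: assumptions.** Two arms of 23. Values are normal with SD 1, and one arm is shifted upwards by *d* SD. Three cuts are tried: above the 97.5th reference percentile, outside ±1.96 SD, and above the 90th percentile.

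**Step 1, proportion abnormal.**
- One-sided cut: p₀ = 1 − Φ(1.96) = 0.025 and p₁ = 1 − Φ(1.96 − d). For d = 0.8, p₁ = 1 − Φ(1.16) = 0.123. Expected abnormal patients: 23 × 0.025 = 0.6 against 23 × 0.123 = 2.8.
- Two-sided cut: p₀ = 0.05 and p₁ = [1 − Φ(1.96 − d)] + Φ(−1.96 − d). For d = 0.8, p₁ = 0.123 + 0.003 = 0.126.

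**Step 2, power of the categorical test.** Sum Bin(a; 23, p₀) × Bin(b; 23, p₁) over all tables (a, b) whose P value is below 0.05, for Fisher and for uncorrected chi-square. This is exact enumeration.

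**Step 3, power of the rank test.** Wilcoxon on the values, by simulation (20,000 runs). As a rough check, the normal approximation for two means at d = 0.8 is Φ(0.8 × √(23/2) − 1.96) = Φ(0.753) = 77%; the rank test comes out slightly lower.

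Power in %, 23 v 23 (Fisher / chi-square):

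| Shift (SD) | Cut at 97.5th percentile | Cut at ±1.96 SD | Cut at 90th percentile | Wilcoxon |
|---|---|---|---|---|
| 0.5 | 1.3 / 4.7 | 1.1 / 3.9 | 11.7 / 19.6 | 36 |
| 0.8 | 8.6 / 19.3 | 5.5 / 12.6 | 33.6 / 45.6 | 72 |
| 1.0 | 21.9 / 37.4 | 14.1 / 25.1 | 54.4 / 66.2 | 90 |
| 1.5 | 75.3 / 85.4 | 60.3 / 72.5 | 93.1 / 96.3 | >99 |

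**Step 4, gain from the baseline value.** Adjusting for baseline divides the residual SD by 1/√(1 − ρ²), where ρ is the correlation between baseline and day 28. Assuming ρ of 0.4 to 0.6, a shift of 0.8 SD acts like 0.8/√0.84 = 0.87 to 0.8/√0.64 = 1.0 SD, and the normal approximation gives Φ(0.87 × 3.391 − 1.96) = 84% to Φ(1.0 × 3.391 − 1.96) = 92%.

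**Compliance rate: assumptions.** 23 patients in each of the two diet arms, 84 meals each (28 days × 3 meals), beta-binomial adherence with precision 5 or 10. Categorical power is for the class DCR ≥ 80%.

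| Mean DCR | Precision | Fisher | Chi-square | Wilcoxon on DCR |
|---|---|---|---|---|
| 85% v 75% | 5 | 29 | 40 | 55 |
| 85% v 75% | 10 | 47 | about 59 | about 76 |
| 90% v 80% | 5 | 33 | 44 | 71 |
| 90% v 80% | 10 | 50 | 62 | 87 |

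**The case against.** Much of the opposing case is sound.

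- *The compliance class is prespecified.* Section 2.12.5 fixes the 80% boundary, and the named test fits a two-class variable. This stands: there is no mismatch, only lost power. A reader might infer that a difference in adherence would mostly be missed. The figures do not support that, since chi-square power is 40 to 62% in the table above. The contrast between the two diet arms is also not the diet's supplementary effect itself, which is diet plus drug against drug alone.
- *Safety is not a lone exception.* A reader might infer that every other measured outcome gets a rank test. It does not: section 2.15 also gives 48-hour transit and percent improvement in symptom scores to chi-square or Fisher.
- *The article states no laboratory cut, and classification is commonly left to a fuller document.* The first half stands, so one cannot criticise the cut itself, nor claim that the baseline value is ignored; a count of new abnormalities would use it. The second half stands less well, because the named test requires classes whatever a fuller document might add.
- *Section 2.15 describes continuous variables and has a general rank-test sentence.* A shift might therefore be visible descriptively. But the specific safety sentence follows, and it lacks the measured/counted split just given to manometry. The general sentence does not clearly override it.
- *The loss can be made to look larger.* Pooling the diet arms to 46 v 46, with Fisher alone and a two-sided cut, widens the gap (at 0.8 SD, 14% against 96%). The article states no such pooling, and it names chi-square first. With a 90th-percentile cut the gap narrows.
- *Small numbers are also to blame.* At 0.5 SD the rank test itself has only 36%. The article acknowledges its small sample.
- *Nothing says that a non-significant test will be read as safety.* Correct. That is a risk to guard against, not a stated intention. Abnormality counts remain a legitimate safety summary.

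**Conclusion.** The point holds for the laboratory values. Section 2.15 names only a categorical test for a safety block that includes measurements taken at baseline and day 28, and it defines no classes for them. With 23 v 23, a shift of 0.8 SD and a cut at the 97.5th percentile or ±1.96 SD, power is about 6 to 19%, against about 72% for a rank test. The shift, the cut and normality are assumptions. At 1.5 SD the categorical test reaches about 60 to 85% under the same cuts, so the loss matters most for moderate shifts.

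For the compliance rate the point is secondary: the test matches the defined class, and the full scale would raise power from about 29–62% to about 55–87% in the assumed scenarios.

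This is worth correcting because the remedy is cheap. It does not affect the primary outcome.

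**What to change.** In section 2.15, replace the single safety and compliance rule with a split like the one used for manometry:

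- Adverse events and counts of abnormal laboratory values: chi-square or Fisher test.
- Each BR and LKF parameter: day-28 value compared between arms with adjustment for its baseline value, or a Wilcoxon or Kruskal–Wallis test on the change, reported as a difference with a 95% confidence interval. The adjusted analysis is preferable where baseline and day-28 values correlate weakly: the change has variance 2(1 − ρ) times that of a single value, so below ρ = 0.5 it is noisier than the day-28 value alone.
- Normal/abnormal tables: keep as description, with the source of the reference limits stated.
- DCR: keep the prespecified 80% class, and also compare the percentage between diet + drug and diet + placebo by Wilcoxon test, with a difference and confidence interval.

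Add a sentence that a non-significant categorical test is not evidence of safety.

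The cost is a change of wording and a few extra analyses of data already planned for collection, with no added patients, visits or tests. The small downside is more laboratory comparisons, so these should be presented as estimates with intervals, not as a list of significance tests.

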### Study design

2.2

The protocol was drafted using the SPIRIT guidelines and the results will be reported following the checklist of the Consolidated Standards of Reporting Trials (CONSORT) statement (see Supplementary Table 1). All the participants will be informed about the study purpose and their signed informed consent will be obtained before joining this parallel-group study. A total of 92 participants will be recruited in each TFC or aTFC subtype following the inclusion and exclusion criteria. Then they will be allocated to drug + diet group, placebo + diet group, drug group and placebo group randomly at 1:1:1:1 ratio. The positive drugs are Macrogol 4000 Powder (Forlax, Beaufort Ipsen Industrie) and Chinese herb powder for TFC and aTFC groups respectively. Outcomes will be evaluated at baseline, the 14th day (followed-up by telephone) and 28th day by researchers blinded to the groups. Participants will be informed whether diet intervention is acted by the enrollment number and obtain the “drug” corresponding to the number, but they and the researchers will not know whether they are receiving a drug or a placebo. The whole study design is illustrated (see Fig. 1). A SPIRIT figure for the schedule of enrolment, interventions and assessments is also presented (see Fig. 2).

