### Randomization, allocation concealment and partly double-blind

2.9

Two groups, each one of 92 independent random numbers, will be generated using Excel 2013 software (Microsoft Corporation, Redmond, Washington) by the third party that does not participate in the study, and will be divided by 4. The remainder will be 1 for group A, 2 for group B, 3 for group C and 0 for group D. A, B, C, D are prescribed as diet + drug, diet + placebo, drug and placebo group, respectively. The number of the drug will be reserved and will be encapsulated and stored in opaque envelopes, preserved by the third party. When a patient is enrolled, an envelope with a sequence number on its surface will be passed to the researchers. The researchers and patients will know whether diet is interfered and the drug number only, but not the corresponding drug or placebo group. When the trial is finished, the third party will uncover the blindness. It is difficult to conduct blinding since the diet intervention is a set of dietary principles, rather than specific food, so only drugs are double-blind to reduce the information bias.

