#### Baseline information

2.12.1

Baseline information will include demographic data and clinical data from the participants after allocation. Demographic data includes gender, age, height, weight, nationality, occupation, and education level. Clinical data includes past medical history, drug allergy history, the history of medications used to treat or induce constipation, dietary habits in the past year (see Supplementary Table 3),^[21]^ the primary outcome and secondary outcomes.

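### The set called ITT requires at least one assessment, and the first assessment comes after the open diet allocation, so early leavers can be excluded in a way that depends on the known arm

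*Protocol article*

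**What the plan says.** Section 2.15 (Planned statistical analysis) opens its rule on analysis sets with "Complying with the intent-to-treat (ITT) and per-protocol (PP) principle" and continues that "all data of the patients randomized and at least 1 assessment (include baseline assessment) will be analyzed". So two conditions apply: randomisation, and at least one assessment, for which baseline suffices. For those who drop out, "their missing data will be obtained by last-observation-carried-forward (LOCF) method".

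The order of events is given elsewhere in the article:

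- Section 2.9, on allocation: "When a patient is enrolled, an envelope with a sequence number on its surface will be passed to the researchers". On what is then known: "The researchers and patients will know whether diet is interfered and the drug number only".
- Section 2.8, on the first data: "After the patients are enrolled, they will finish a questionnaire (baseline information) and the relevant examinations".
- Section 2.12.1, on their timing: "Baseline information will include demographic data and clinical data from the participants after allocation". The clinical data listed there include the primary outcome.
- Section 2.2, on the assessments: "Outcomes will be evaluated at baseline, the 14th day (followed-up by telephone) and 28th day by researchers blinded to the groups".

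Section 2.12.2 counts treatment as effective when CSBM per week rises by at least 1. Section 2.6 plans 23 participants per arm and 92 per subtype, with no assumed effect, response rate or dropout rate.

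**The concern.** Requiring one assessment is usually harmless, because baseline is taken before randomisation and everyone has it. Here baseline follows an allocation whose diet part is open. Whether a patient enters the set is therefore settled after randomisation, by people who know whether the diet applies.

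The two sides have different reasons to leave at that moment. Patients in the diet arms learn that they must avoid meat, eggs, milk, coffee and fried food for 28 days. Patients in the other arms learn that they keep their usual eating habits, which may disappoint someone who joined a diet trial for the diet. Either kind of leaver disappears from the analysis if no baseline was recorded.

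The effect of the diet is the trial's stated objective (section 2.1), so the comparison exposed is the main one. Comparisons of drug with placebo within the same diet condition are not exposed in this way, since the drug is blinded and none has yet been taken.

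**Working it through.** **Which patients are lost.** Set the sections against each point at which a patient might leave:

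| Patient leaves | Assessment on record | In the set? | Outcome used |
|---|---|---|---|
| After the envelope, before the baseline questionnaire | none | no | none |
| After baseline, before day 14 | baseline | yes | baseline carried forward: change 0, not effective |
| After day 14 | baseline and day 14 | yes | day 14 carried forward |

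Only the first row is affected.

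**The plan's own figures.** The only arithmetic to reproduce is 4 × 23 = 92, which agrees. The article gives no power calculation or expected loss.

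**Illustration of size.** Inputs from the article: n = 23 per arm (section 2.6), the responder rule (section 2.12.2) and LOCF (section 2.15). Assumed inputs: responder rates among those kept of p_d = 60% with diet and p_c = 40% without, and one to three leavers before baseline. Leavers are counted as non-responders, which is how LOCF already treats someone with baseline only.

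With k_d leavers in the diet arm and k_c in the no-diet arm:

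- planned set: difference = p_d − p_c = 20.0 points
- all randomised: difference = p_d(n − k_d)/n − p_c(n − k_c)/n
- shift (planned set minus all randomised) = p_d·k_d/n − p_c·k_c/n

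| Leavers | All randomised, points | Shift, points |
|---|---|---|
| 1 diet | 0.6 × 22/23 − 0.4 = 17.4 | 0.6 × 1/23 = +2.6 |
| 2 diet | 14.8 | +5.2 |
| 3 diet | 12.2 | 0.6 × 3/23 = +7.8 |
| 1 no-diet | 0.6 − 0.4 × 22/23 = 21.7 | −0.4 × 1/23 = −1.7 |
| 2 no-diet | 23.5 | −3.5 |
| 3 no-diet | 25.2 | −0.4 × 3/23 = −5.2 |
| 2 diet and 2 no-diet | 18.3 | +1.7 |

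If the two diet arms of a subtype are pooled against the two no-diet arms (46 v 46), one to three diet leavers give +1.3, +2.6 and +3.9 points.

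**Sensitivity to the leavers' outcome.** Suppose diet leavers would have responded like the no-diet arm. The shift is then k/n × (60% − 40%), that is 0.9, 1.7 and 2.6 points for one, two and three of 23. If they would have responded like those who stay, it is 0.

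**The case against.** Much of the case on the other side stands.

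- **The window may be short.** Experts have already judged eligibility and consent has been signed (section 2.7), and the questionnaire follows enrolment. Few patients may leave in between. The schedule figure and Table 1 were not available in the text reviewed and might give a finer order. But section 2.12.1 states outright that baseline follows allocation, so a figure showing the reverse would itself need reconciling.
- **Most refusers are kept.** A reader might infer that the diet arms would retain only patients willing to start the diet. That does not follow. Baseline counts as an assessment, so someone who completes it and then refuses the first diet meal stays in, with no change carried forward.
- **The direction is not fixed.** A reader might infer that the diet effect is bound to be overstated. No section says who would leave early or from which arm. The introduction cites a survey in which most constipated adults preferred lifestyle and dietary change, so disappointed no-diet patients are a real possibility, and their loss biases the other way.
- **The trial is exploratory and small.** That lowers the stakes. It does not justify giving the name ITT to a set selected after randomisation, especially when section 3 expects reliable evidence of dietary efficacy.

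What survives is the rule itself: as written, it lets an arm-dependent event decide who is analysed.

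**Conclusion.** The concern holds in a limited form. Section 2.15 claims ITT, yet its set omits randomised patients with no assessment. Sections 2.9 and 2.12.1 together place the first assessment after an open diet allocation. The diet comparison may be biased: in favour of diet if refusers cluster in the diet arms and would do worse than those who stay, and against it if losses come from the no-diet arms.

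The size is unknown. Under the assumed 60% v 40%, with 23 per arm and one to three leavers counted as non-responders, the shift runs from −5.2 to +7.8 points according to which arm loses them. It can be zero.

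A reader might also scale the effect by 1/(1 − p) for an assumed early loss p in the diet arm alone; 1 to 5 of 23 would give 5% to 28%. The documents support neither that loss nor its one-sidedness. The factor also describes a difference in means, whereas section 2.15 uses rank tests for CSBM.

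The change is worth making because the rule is explicit, the comparison affected is the main one, and the repair is cheap.

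**What to change.** 1. In sections 2.8, 2.9 and 2.12.1, have the baseline questionnaire and examinations completed before the envelope is opened. Every randomised patient then has an assessment and the condition excludes nobody.
2. In section 2.15, define the ITT set as all randomised patients in their allocated arm, with no assessment condition. Count a patient without any assessment as not effective under section 2.12.2, with a change of zero in CSBM per week. The same reading should apply to both forms of the outcome. Borrowing values from the arm with the same drug and no diet would not do: such a patient may have taken no drug either, and would be a failure on one scale and an average patient on the other.
3. Report, by arm, how many patients withdrew between the envelope and the first assessment.
4. Call any set that requires an assessment modified, and use it only as a sensitivity analysis.

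Section 2.10 separately removes emergency-unblinded patients from the efficacy analysis. It must be reconciled with whatever definition of ITT section 2.15 adopts.

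The cost is a few sentences and a change in the order of two steps at enrolment. Examinations would be done on some patients who then decline randomisation. The estimated diet effect may come out slightly smaller. If recruitment has already begun and the order cannot be changed, items 2 to 4 still apply.
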